## Abstract

Acute bronchiolitis is a common respiratory infection that affects approximately 30% of children under two years of age in France. While most cases are mild and treated on an outpatient basis, around 0.5% of children require hospitalization for monitoring and/or treatment. This condition, which is linked to various respiratory pathogens, accounts for a significant proportion of winter activity in hospital pediatric departments. Diagnosis for young children under two years of age is currently based on nasopharyngeal aspiration (NPA), performed by nurses on medical prescription. Although considered the gold standard, this technique is invasive and potentially traumatic for children. It often requires several caregivers and sometimes causes tension with families. The experience of the SARS-CoV-2 pandemic has highlighted the value of saliva sampling, with good diagnostic concordance with reference methods, as well as better tolerance and acceptability than nasopharyngeal swabbing in children over 2 years of age. In this context, our study aims to compare NPA and saliva sampling in the diagnosis of respiratory distress in children between 28 days and 2 years of age, to evaluate the concordance of results, and to compare tolerance and acceptability. Clinical trial number: NCT07350291.

**Specifications table**

**Table utbl0001:** 

**Subject area**	Medicine and Dentistry
**More specific subject area**	Pediatric respiratory virology
**Name of your protocol**	Evaluation of the diagnostic capabilities of saliva samples from pediatric patients with respiratory symptoms, promoting the active involvement of the individuals concerned and their families: a randomized, intra-individual study.
**Reagents/tools**	Saliva collection tube: ORACOL+ (Malvern Medical, Worcester, UK) Mucus suction device (40mL), suction catheter appropriate for the child's age (ch6/8) qPCR reagents: Alinity m Resp-4-Plex Assay (Abbott Molecular Diagnostics, Abbott Park, Illinois, USA); AllPlex Respiratory Panels Assays 2, 3 and PneumoBacter (Seegene Inc, Seoul, South Korea)
**Experimental design**	Bronchiolitis is a common viral respiratory infection in children under 2 years of age and is responsible for a significant number of hospitalizations. This study aims to evaluate the reliability and comfort of a noninvasive saliva sample for detecting respiratory pathogens in infants with bronchiolitis. The project will be based on intra-individual randomization (crossover) of 502 children at the University Hospital of Poitiers. Each patient will undergo both sampling techniques; randomization will determine the order in which the samples are taken.
**Trial registration**	This study was registered in the Clinical Trial Registry (NCT07350291)
**Ethics**	This research will respect the principles and foundations of the Helsinki Declaration and Good Clinical Practice. It will also be registered with a personal data protection committee in accordance with current French legislation prior to any recruitment. The results of this study will be disseminated through presentations at scientific conferences and publication in peer-reviewed journals.
**Value of the Protocol**	Most studies were retrospective. This proposal is the first to prospectively evaluate the feasibility and performance of saliva sampling for the etiological diagnosis of respiratory distress in children under the age of two. Randomizing the order of the sampling techniques will help reduce bias due to confounders, even if the first sample could influence the quality of the second. If diagnostic concordance with nasopharyngeal aspirate (NPA) is demonstrated, this method could offer a noninvasive and better-tolerated alternative, with several potential advantages: - For the child and their family: reduced pain, reduced parental stress. - For caregivers: reduced risk of splashing or contact with nasal secretions, greater acceptability of the procedure. - For healthcare organizations: speed, simplicity, and the possibility of use outside the hospital (community medicine, nurseries, population screening).

## Background

Bronchiolitis is a common viral respiratory infection in children under 2 years of age and is responsible for a significant number of hospitalizations each winter. While respiratory syncytial virus (RSV) is the most common agent, accounting for 50–80% of cases, other viruses have been recognized as responsible for bronchiolitis [1]. Indeed, since the rise of molecular biology, almost all common respiratory viral etiologies have been implicated in bronchiolitis, including human rhinovirus and enterovirus, human metapneumovirus, parainfluenza virus, seasonal coronaviruses and SARS-CoV-2, adenovirus, and influenza A/B, without clinical differentiation from RSV infection. Moderate cases require monitoring and oxygen or fluid support, while 2–6% of infants develop a severe form requiring intensive care. Unfortunately, no clinical score or clinical sign can predict the evolution of bronchiolitis. Diagnosis is based on clinical examination, usually accompanied by nasopharyngeal swabs (NP) or nasopharyngeal aspirate (NPA). Nasopharyngeal aspirate, generally performed in children under the age of two, is the most used sampling method but remains invasive, causes discomfort, and is time-consuming. This highlights the need for innovative approaches to improve the care and comfort of infants who must undergo virological testing. Salivary samples have been widely used during the SARS-CoV-2 pandemic in multiple settings, including infants and adults, healthcare workers, and symptomatic or asymptomatic patients [2,3].

In adults, saliva sampling is less invasive and can be self-collected, improving the acceptability of respiratory screening [3,4]. In children, saliva sampling was used during the pandemic for mass screening in schools and asymptomatic screening and can be either self-collected or retrieved with swabs or sponges [2,5]. While diagnostic performance was mainly evaluated for the detection of SARS-CoV-2, almost all other respiratory pathogens have been detected using saliva. These results were highly influenced by the type of saliva sampling (swabbing the oral cavity, drooling, using specific sponge-swabs for 30 seconds to one minute), the pre-analytical attention paid to saliva sampling (guidance on not eating, drinking, or performing oral hygiene 30 minutes before sampling; paying attention to a minimal volume collected), and the population (symptomatic or asymptomatic) [6,7]. Moreover, most studies were retrospective, and selection of patients was based on the results of NPA or NP swabs. Overall, the sensitivity and specificity of saliva sampling seem close, if not equivalent, to NP in adults. However, few studies have been conducted in children under the age of 2, specifically in the context of acute bronchiolitis.

Thus, the present study aims to evaluate the overall agreement of saliva sampling in children under 2 presenting to a university hospital with respiratory symptoms, compared to NPA. Secondary objectives are to evaluate the diagnostic performance of NPA versus saliva sampling for each respiratory pathogen, and to compare the reliability and comfort.

## Description of protocol

### Study design

The PreSap study is a publicly funded, national, prospective, monocentric, randomized clinical trial comparing saliva samples and NPA in children between 28 days and 2 years old (Fig. 1). Once the protocol has been explained to the parents and child, and their agreement has been received, all patients will undergo the two sampling procedures after a randomization determining the order (crossover design with a 1:1 ratio). Randomization will be carried out with the REDCap software. Depending on the randomization, the saliva sample will be taken first or second, and the same will be done for the NPA. A rest period will be allowed between each sample so that the child can be calm again for the second sample. All temporal and behavioral data will be recorded.

**Fig. 1 fig0001:**
[figure not shown]
Study design. NPA: nasopharyngeal aspirate.

### Study population

Recruitment is performed during a visit to the pediatric emergency department or during hospitalization in the pediatric department of the University Hospital of Poitiers, France. Inclusion criteria are: a) age between 28 days and 2 years; b) respiratory symptoms requiring an etiologic diagnosis as part of routine care; c) consent of both parents; d) affiliation with the social security system; e) no contraindication to either of the two sampling procedures (hemophilia, anticoagulant therapy, thrombocytopenia, risk of epistaxis, hypertrophic rhinitis, life-threatening emergencies, food, drink or oral care before the test (30 minutes), nasal antigen test already done in pediatric emergencies during this hospital stay and patient already included in the PreSap study).

### Ethical approval and registration

All procedures will be explained to the parents, and an informed consent form will be completed and signed. This study is registered in the Clinical Trial Registry (NCT07350291). The study protocol will be submitted to an institutional ethics committee and must be approved before any participants are enrolled.

### Experimental intervention

NPA will be performed as described in the recommendations of the French Pediatric Society [8]. The component used at Poitiers University Hospital is the Poly Medicure mucus extractor (mucus suction device with suction catheter) without transport medium. A minimum volume of 1.5 mL is required. This procedure is performed by a trained caregiver.

### Control intervention

Salivary samples will be obtained using a sponge swab (ORACOL+, Malvern Medical, Worcester, UK). These medical devices do not contain transport medium. Saliva should be collected without having eaten or drunk, or performed a mouthwash in the previous 30 min. Sponge swabs must be kept in the oral cavity for 30 sec to 1 min to obtain between 200 and 500 µL of saliva. This procedure can be performed by a caregiver or by the parents after they have been given the necessary instructions.

### Sending sample to the laboratory

All matched samples (NPA and saliva) will be sent at room temperature to the virology laboratory. If the analyses are not performed immediately, the samples will be stored at +4°C. The sponge swabs will be centrifuged as recommended by the manufacturer to collect saliva in the dedicated microtube.

### Primary outcome measure

To assess substitutability, the primary outcome will be overall agreement, i.e., a patient with a saliva-based test that diagnoses the same pathogens as the NPA-based test. Samples will be analyzed using the Alinity m Resp-4-Plex Assay (Abbott Molecular Diagnostics, Abbott Park, Illinois, USA) and AllPlex Respiratory Panels Assays 2, 3, and PneumoBacter (Seegene Inc., Seoul, South Korea). These assays allow the detection of flu A and B; SARS-CoV-2; RSV (A and B without distinction); adenovirus; enterovirus; metapneumovirus; parainfluenza (1 to 4 with differentiation); bocavirus (1 to 4 without distinction); coronavirus 229E; coronavirus NL63; coronavirus OC43; rhinovirus; *Bordetella parapertussis; Bordetella pertussis; Chlamydophila pneumoniae*; and *Mycoplasma pneumoniae*. All these assays use an exogenous internal control to ensure proper extraction, amplification, and the absence of PCR inhibitors.

Both samples will be analyzed at the same time to compare the results on fresh samples. Quantitative PCR analysis will be fully automated on all assays. However, only the NPA result will be visible to clinicians to avoid interfering with the study. In case of invalid results, samples will be tested a second time, possibly diluted if PCR inhibitors are suspected. All dilutions of a sample will be noted in the final analysis to ensure an unbiased comparison. Assays used in this study have not been approved for the saliva matrix, but use the same extraction protocol that has been validated on SARS-CoV-2 assays [9,10]**.**

### Secondary outcome measures

Secondary evaluation criteria are defined as follows:a)Performance of saliva sampling compared to NPA for each pathogen detection (qualitative; semi-quantitative using cycle threshold (Ct) values).b)Pain related to each sampling technique using the EVENDOL (EValuation ENfant DOuLeur; Evaluation Child Pain), a recognized and validated standardized pain assessment scale for children under 7 years of age [11]. It will be assessed by the caregiver.c)Caregiver and parental satisfaction related to each sampling technique using a 0–10 visual scale.d)Time spent by caregivers for each procedure (without considering the time needed for preparation and explanation).e)Complications associated with the sampling techniques: bleeding, irritation, and exposure of healthcare workers to biological agents.f)Procedural discrepancies associated with the two sampling techniques: involvement of multiple healthcare workers, repetition of the procedure, and cessation of care by the legal representative.g)Non-conclusive results according to the sampling technique: insufficient sample volume, refusal of sampling, and laboratory measurement errors.

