### Data acquisition

Data acquisition will be carried out by investigators or clinical research assistants using electronic case report software. The following data will be collected: age (in months), sex, medical history requiring consultation or hospitalization, time since the onset of respiratory symptoms, Silverman score, fever, use of anticoagulants, time required for each respiratory sample (NPA and saliva), immediate complications of each respiratory sample, failure to retrieve one sample, number of caregivers required for each respiratory sample, help from parents required for one of the respiratory samples, procedural discrepancies, pathogens detected, cycle threshold value for each pathogen, satisfaction of caregivers and parents using a 0–10 visual scale, and pain assessed during each procedure using the EVENDOL scale.

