### Data analysis

The type I risk will be 5% for all analyses. The 95% confidence intervals (CI) will be estimated by non-parametric bootstrapping (1,000 resampling), especially because of the low prevalences of pathogens and the related non-gaussian distributions. No interim analyses are planned. No correction of the multiplicity of tests will be performed. The analysis of the secondary endpoints will therefore be considered exploratory.

Because we expect a low percentage of missing values and missingness is at random, complete case analyses will be performed, i.e., patients with a missing value on the NPA-based test or the saliva-based test will not be considered in the analyses. The baseline characteristics (listed in the previous subsection) of the excluded patients will be compared with those of the analyzed population. If we observe differences, i.e., a non-random process, the outcomes’ analyses will be based on multiple imputation to reduce the risk of bias due to missingness (50 imputed databases, and confidence intervals obtained from the 5,000 resulting bootstrap samples).

*Descriptive analysis.* A description of demographic and clinical characteristics will be provided using means and standard deviations for continuous characteristics, or percentages and effectives for categorical characteristics. This description will be performed for the overall sample and according to the overall agreement (primary outcome) of the saliva-based and the the NPA-based tests.

*Analysis of the primary outcome.* We will estimate proportion of overall agreement and the related 95% CI. The agreement will be the diagnostic the same pathogens in-between the NPA-based and the saliva-based tests. More precisely, consider the following table for a pathogen where . The overall agreement is defined as

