**Table utbl0002:** 

Effective (proportion)		Saliva-based test		Total
		Positive result	Negative result	
NPA-based test	Positive result	()	()	()
	Negative result	()	()	()
	Total	()	()	()

*Analysis of the secondary outcomes (a).* For each pathogen, the following estimations and related 95%CI will also be estimated with the use of NPA-based results as gold standards [13]. The positive and negative percent agreement are respectively equaled to and . The Cohen’s kappa coefficient is, where . Additionally, by considering the NPA-based as the reference, sensitivity and specificity are .and, respectively. In addition, positive and negative predictive values are and, respectively.

*Secondary outcomes (b-d).* The pain level, the parental satisfaction, and the time spent by caregivers will be compared according to the sampling technique (NPA versus Saliva) in terms of means by paired two-sample t-tests. The interaction with the order (saliva/NPA or NPA/saliva) will also be explored by mixed linear models.

*Secondary outcomes (e-g).* The causes of complications, procedural discrepancies, and non-conclusive results will be described in terms of frequencies and percentages. In addition, to compare the two techniques, the following three proportions will be estimated and compared by using McNemar test: i) the proportion of sampling with at least one event among the following complications: bleeding, irritation, and exposure of healthcare workers to biological agents; ii) the proportion of sampling which has necessitated multiple healthcare workers, repeated procedure, or cessation of care by the legal representative; iii) the proportion of interventions with non-conclusive results: insufficient sample volume, refusal of sampling, or laboratory measurement errors. The interaction with the order (saliva/NPA or NPA/saliva) will also be explored by mixed logistic models.

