### Strengths of the protocol

The present single-center, open-label, intraindividual trial will be carried out as soon as regulatory approvals have been obtained and will take place over three years at Poitiers Hospital, starting in winter 2026.

The literature is mostly composed of retrospective studies with potential selection bias due to the inclusion of patients who tested positive for a pathogen with the reference method [5,14]. Moreover, the sample sizes were often limited, as were the pathogens sought. The assessment of patients' pain and comfort was often neglected. The main strengths of our protocol compared to this literature are its focus on infants under 2 years of age, a population for which high-quality sampling is difficult to achieve. We propose a prospective crossover design in a clinical setting that enables a reliable performance comparison between the two procedures, limiting biases. If the primary objective is fulfilled, saliva sampling may be considered the first-line sample for respiratory diagnostics in children under 2 years in our hospital.

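### Pain and caregiver time are tested as one independent difference per child; if the NPA-versus-saliva difference varies between caregivers, precision is overstated, and the listed data do not identify the caregiver

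*Protocol article*

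**What the plan says.** Under Secondary outcome measures, the Protocol article makes pain on the EVENDOL scale outcome (b) and says "It will be assessed by the caregiver". Outcome (c) is caregiver and parental satisfaction, and outcome (d) is the time caregivers spend on each procedure. For the NPA, Experimental intervention states "This procedure is performed by a trained caregiver". Under Control intervention, either a caregiver or the parents may take the saliva sample. Strengths of the protocol describes "The present single-center, open-label, intraindividual trial", running for three years at one hospital.

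The analysis of outcomes (b) to (d) reads "The pain level, the parental satisfaction, and the time spent by caregivers will be compared according to the sampling technique", and this is done "in terms of means by paired two-sample t-tests". Mixed linear models are mentioned only to explore the interaction with sampling order, and their grouping level is not given. Data analysis adds "The type I risk will be 5% for all analyses", announces bootstrap confidence intervals without naming the resampling unit, and declares the secondary endpoints exploratory. The only listed data item on staffing is "number of caregivers required for each respiratory sample" (Data acquisition), apart from parental help.

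**The concern.** A paired t-test needs the within-child differences to be independent of one another. Here hospital staff produce the measurements: they score pain knowing which technique was used, and the time is their own. If one nurse is quicker with the suction catheter, or tends to score the sponge swab as gentler, all of that nurse's children share this tilt. The differences are then correlated within caregiver, and the effective number of observations is below the number of children.

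The abstract makes tolerance and acceptability an aim of the study, and the section on the value of the protocol lists less pain and better acceptability among the gains hoped for from saliva. Pain and caregiver time bear directly on that claim, so overstated precision would make it look firmer than it is. If nobody records who performed or scored each sample, the clustering can be neither measured nor corrected afterwards.

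**Working it through.** **The plan's own figure.** The sample size concerns the primary agreement outcome: 1.96² × 0.95 × 0.05 / 0.02² = 456.17, rounded up to 457 analysed. Then 456.17 × 1.10 = 501.8, rounded up to 502 included. Both figures reproduce, and this point does not touch them. No power or sample size is stated for outcomes (b) to (d).

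**Inputs.** From the Protocol article: 457 analysable children and a type I risk of 5%, taken here as two-sided because sidedness is not stated. Not in the article, therefore assumed: the number of caregivers K, and the intra-caregiver correlation (ICC) of the within-child NPA-minus-saliva difference.

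**Formulas.** With equal numbers of children per caregiver, m = 457/K:

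- design effect DE = 1 + (m − 1) × ICC
- the confidence interval should be wider by the factor √DE
- actual two-sided error = 2 × (1 − Φ(1.96/√DE))

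Example with K = 60 and ICC = 0.05: m = 7.62, DE = 1 + 6.62 × 0.05 = 1.33, √DE = 1.15, 1.96/√DE = 1.70, error = 8.9%.

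**Results at ICC 0.05**

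| Caregivers | Children each | DE | CI should be wider by | Actual error |
|---|---|---|---|---|
| 20 | 22.9 | 2.09 | 45% | 17.5% |
| 30 | 15.2 | 1.71 | 31% | 13.4% |
| 60 | 7.6 | 1.33 | 15% | 8.9% |
| 150 | 3.0 | 1.10 | 5% | 6.2% |

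**Other correlations.** At ICC 0 the error is 5% for any K. At ICC 0.01 it is 7.6% with 20 caregivers and 5.2% with 150. At ICC 0.10 it is 27.2% and 7.4%.

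**Check by simulation** (paired t-test, 457 children, 4,000 runs per setting):

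- A caregiver effect common to both techniques, 20% of the variance, left the error at 4.7% to 5.3% with 20, 40 or 80 caregivers. This held whether one caregiver handled both samples or different caregivers were assigned at random.
- A technique difference varying between caregivers, with ICC 0.05, gave 17.6%, 12.4% and 8.4% for 20, 40 and 80 caregivers. The formula gives 17.5%, 11.2% and 7.8%.

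Repeated use of the same caregivers therefore does no harm in itself. Only variation between caregivers in the technique difference does.

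**The case against.** The strongest reply is that nothing in the article places the trial inside the harmful range. Recruitment spans the emergency and inpatient paediatric departments over three years, so the pool of caregivers may be large, and with 150 of them the effect is about one percentage point at ICC 0.05. No evidence is given that the technique difference varies between staff. This stands, and it is why the point is conditional. A reader might infer that the intervals are too narrow as a matter of fact, but the documents do not support that.

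Two other stronger readings also fail. A reader might name caregiver satisfaction as the worst case, but the analysis section names only parental satisfaction, so no analysis of caregiver satisfaction is stated that could be wrong. A reader might also assume a bootstrap over children, but the resampling unit is not given.

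Next, the random-effect structure may sit in an analysis plan that is not shown. That is fair for the model. But the paired t-test is a stated choice, and no analysis plan can recover a caregiver's identity that was never recorded. The full case report form, also not shown, may hold such a field; the published list does not.

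Finally, if the target is the average difference among this hospital's present staff, caregivers can be treated as fixed, and the child-level test is then not anti-conservative. That is a legitimate target, and the article does speak of use in its own hospital. But it also looks to a multicentre successor and to use outside hospital, where variation between caregivers belongs in the uncertainty.

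**Conclusion.** The point holds in a conditional form and is minor. For pain and caregiver time, the stated test assumes independence between children that shared caregivers may break, and the listed data would not allow anyone to find out. The error rate runs from the nominal 5% upward: about 6%, 9% and 18% with 150, 60 and 20 caregivers, assuming 457 children, equal workloads and an ICC of 0.05 for the within-child difference. Both the number of caregivers and the ICC are assumptions. That the same staff recur is an inference from one hospital and 502 children, though a safe one.

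Parental satisfaction is not in question on this ground, because each child's own parents give the rating. The primary outcome, agreement of automated PCR results, is unaffected. The secondary endpoints are declared exploratory, which limits the consequence but does not correct an interval of the wrong width.

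**What to change.** In Data acquisition, add for each sample a pseudonymous code for the main performer, with a category for a parent in the case of saliva, and a separate code for the person who scores pain. One field is not enough, because a sample may involve several caregivers or a parent, and the scorer need not be the performer.

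In the analysis of outcomes (b) to (d), report the technique difference in pain and caregiver time from a mixed model with child and caregiver effects, including a caregiver-by-technique random effect. Caregiver-clustered standard errors with a small-sample correction are an alternative. This should stand at least as a sensitivity analysis beside the paired t-test. A random intercept for the child alone would not address the problem. If an analysis of caregiver satisfaction is added, the same clustering applies.

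The cost is a few coded fields, a sentence or two in the analysis section, and possibly wider intervals for exploratory outcomes. The codes must be in place before enrolment. The article describes ethics submission as still to come and a start in winter 2026.
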